### Procedure for unblinding if needed {17b}

An Emergency Code Break will be available to the investigator. This Code Break should be opened only in emergency situations when the identity of the intervention must be known by the investigator in order to provide appropriate medical treatment.

## Data collection and management

### Plans for assessment and collection of outcomes {18a}

Given the study’s longitudinal design, including constant and periodic assessments, data will be constantly evaluated.

The assessors are the researchers of the study. They are trained to perform standardized care, the way of approaching the participant and carrying out the assessment and directions during treatment.

The questionnaires are answered without the presence of the evaluator and without a time limit, so that the answer is not influenced by external factors. Likewise, all questionnaires used in the study are validated and consolidated in the literature.

PM will be performed twice in order to increase the reliability of the critical tinnitus frequency matchings.

### Plans to promote participant retention and complete follow-up {18b}

No specific plans to promote participant retention are implemented in this trial. As this is a trial involving treatment for a symptom that so far has no cure, participant retention is not usually an issue in the treatment phase.

As the treatment is over an extended period of time, it is possible that sessions may be forgotten or forms not filled out and, in these cases, participants will be contacted by phone and email.

### Data management {19}

The data is organized in a pseudonymization allocation list. Each participant receives one code after the randomization, generated by a computer program, which will be used throughout the trial. The participants will be informed about this procedure before starting the data collection. Participant data may only be reviewed by authorized persons on the research team or other authorized people to verify that the study is being accomplished correctly. All persons authorized will have a duty of confidentiality.

All collected data are answered online on a secure platform, then stored in computer files protected by the IT department of University Hospital Zurich. The pseudonymization allocation list is kept separate from the pseudonymized data, by the biometrician, and deleted upon completion of the trial. Data are kept for 10 years before being deleted.

### Confidentiality {27}

The investigators will treat the entire body of information related to the study and the compiled data strictly confidentially. Any forwarding of information to persons not directly involved in the study must be approved by the owner of the information.

Data generation, transmission, archiving, and analysis of personal data within this study strictly follows the current Swiss legal requirements for data protection. A prerequisite is the voluntary approval of the participant given by signing the informed consent form prior to the start of participation in the clinical trial.

The participant medical information obtained for the study is confidential. Participant’s confidentiality will be further ensured by utilizing participant identification code numbers to correspond to treatment data in the computer files.

Such medical information may be given to the participant’s personal physician or to other appropriate medical personnel responsible for the participant’s welfare, if the participants have given their written consent to do so.

Data generated as a result of this study will be available for inspection on request by the monitors and by the Competent Ethics Committee.

### Plans for collection, laboratory evaluation, and storage of biological specimens for genetic or molecular analysis in this trial/future use {33}

This is not applicable, no samples collected.

## Statistical methods

### Statistical methods for primary and secondary outcomes {20a}

The distributions of the data will be assessed using measures of central tendency and measures of dispersion to determine the characteristics of tinnitus and describe other variables associated with the symptom.

The descriptive tinnitus data will be presented in tables, separated by intervention group. The safety parameters, adverse events, and laboratory assessments will be listed by participants and displayed in summary tables.

Finally, the assumptions of the independent and dependent variables will be evaluated. Parametric or non-parametric tests will be chosen based on the features of the data. These tests include the verification of absence of outliers through boxplot; homogeneity of variances in the independent variables through Levene test; and Mauchly’s test for sphericity, or if necessary, Greenhouse Geisser corrections.

The analysis will be performed using the statistic program R (https://www.r-project.org).

#### Primary analysis

The data will be statistically analyzed for changes in subjective tinnitus loudness and distress (VAS) and MML by means of frequentist linear mixed-effect modelling (LME) by the biometrician after data collection has been completed.

Between- and within-subjects repeated measures ANOVA will be used to compare the effect of treatment pre and post, in both intervention groups.

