The second block of the study consists of Treatment Period 2 and Follow-up 2. This block has the same characteristics in the procedure and performance time as the previous sessions (from 2 to 13), the difference is the type of stimulation of HD-tRNS, which contrasts with the one previously carried out (Active/Sham). In session 14, the second period of treatment starts, and the same assessments are made as in session 2. Sessions 15–22 are treatment sessions. In session 23, the same assessments are made as in session 11. Follow-up 2 occurs in sessions 24 and 25, with the same characteristics as follow-up 1 (Fig. 4).

The Close-out is performed in session 26, 7 days after Follow-up 2 and approximately 1 month after Treatment 2 (Fig. 4). In this last session, the primary, secondary, and other outcome measures are performed.

The intervention and evaluation procedures, as well as the explanations regarding the choice of paradigms, can be found in detail below:

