### Outcomes {12}

#### Primary outcome

There are three primary outcome measures in the study. Two of them assessed by means of behavioral self-report, visual analog scale (VAS) ratings of tinnitus for loudness and distress [72], and the third is performed by measuring the MML.

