### Participant timeline {13}

Participants will receive 20 days of therapy, 10 days with active current, and 10 days sham stimulation.

Before each block, primary, secondary, and other outcomes will be assessed. In addition, two follow-ups will be performed, with 2 days of assessments each. Finally, there will be a close-out, with complete evaluation of all outcomes (Fig. 4).

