### Sample size {14}

Sample size calculations were conducted in G*Power 3.1.9 for the repeated measures, within-between interaction (ANOVA). The total sample size needed to detect a high assessment-by-treatment interaction effect (*f* = 0.25, beta = 0.95, alpha = .05, groups = 2, measurements = 5) is 32 participants. However, to compensate for a high estimated dropout rate of up to 25% during treatment, the aim is to recruit 40 participants leading to 20 participants per group.

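### The pre/post ANOVA named as a primary analysis is a change-score test; between arms, adjusting for the session 2 baseline is more efficient

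*Protocol article*

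**What the plan says.** Statistical methods {20a}, Primary analysis, names two methods. The first sentence reads "The data will be statistically analyzed for changes in subjective tinnitus loudness and distress (VAS) and MML", to be done "by means of frequentist linear mixed-effect modelling (LME) by the biometrician after data collection has been completed". It lists no fixed effects, random effects or covariates. The second sentence reads "Between- and within-subjects repeated measures ANOVA will be used to compare the effect of treatment pre and post, in both intervention groups". It names no covariate either.

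The outcomes section says "There are three primary outcome measures in the study": VAS loudness, VAS distress and MML. Baselines for them exist. Participant timeline {13} states "Before each block, primary, secondary, and other outcomes will be assessed", and Intervention description {11a} adds "In session 14, the second period of treatment starts, and the same assessments are made as in session 2". Session 2 therefore precedes all treatment, while session 14 comes after block 1 treatment and its follow-up.

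Sample size {14} uses the G*Power repeated measures within-between interaction with f = 0.25 and "beta = 0.95, alpha = .05, groups = 2, measurements = 5) is 32 participants"; 40 are to be recruited. No correlation among the measurements is printed.

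**The concern.** In a mixed ANOVA with pre and post as the two levels, the group-by-time F is the square of the two-sample t on post minus pre. The baseline is part of the response with its coefficient fixed at 1, so its full error enters the contrast. A baseline covariate has its coefficient estimated from the data, which in a randomised between-arm comparison targets the same effect with less variance.

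At stake is precision in a trial of at most 40 participants, for the comparison of bimodal stimulation with HD-tRNS alone. This is a question of efficiency. The change-score test is not invalid.

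**Working it through.** **Inputs.** From Sample size {14}: f = 0.25, alpha 0.05, 2 groups, 5 measurements, N = 32 (40 recruited), and 0.95, which is labelled beta and read here as power. Assumed: the correlation rho, equal pre and post variances, and sphericity.

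**1. The stated sample size.** For the within-between interaction, lambda = f² × N × m / (1 − rho), with df 4 and (N − 2) × 4. At rho = 0.5 and N = 32, lambda = 0.0625 × 32 × 5 / 0.5 = 20 with df 4 and 120, giving power 95.7%. N = 30 gives 94.3%. So 32 reproduces at rho = 0.5. By contrast, rho 0.3 needs 44, 0.6 needs 26 and 0.7 needs 20. I therefore take 0.5 as the central assumption and show a range.

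**2. Effect size for a pre/post comparison.** With two groups and two levels, f = 0.25 means interaction terms of ±0.25 SD in four cells. That is a difference in change of 4 × 0.25 = 1 SD between arms.

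**3. Between-arm variance per participant, in SD² units.** Change score: 2(1 − rho). Adjusted for baseline: 1 − rho². The ratio is (1 − rho)(1 + rho) / [2(1 − rho)] = (1 + rho)/2.

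**4. Power at N = 32.** lambda = N × 1² / (4V) = 8/V, with df 1 and 30 for change, 1 and 29 for adjusted.

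| rho | V change | V adjusted | ratio | lambda change | lambda adjusted | power change | power adjusted | gain (points) |
|---|---|---|---|---|---|---|---|---|
| 0.3 | 1.40 | 0.91 | 0.65 | 5.71 | 8.79 | 63.8% | 81.7% | 17.9 |
| 0.5 | 1.00 | 0.75 | 0.75 | 8.00 | 10.67 | 78.1% | 88.4% | 10.3 |
| 0.7 | 0.60 | 0.51 | 0.85 | 13.33 | 15.69 | 94.2% | 96.9% | 2.7 |
| 0.8 | 0.40 | 0.36 | 0.90 | 20.00 | 22.22 | 99.1% | 99.5% | 0.4 |

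A simulation with 8,000 trials per setting gave 78.5% and 87.3% at rho 0.5, and 64.4% and 81.3% at rho 0.3. At N = 40 and rho 0.5 the formulas give 86.9% and 94.5%.

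**5. Active versus sham within participant.** Let r1 be the pre-post correlation within a block and r2 the correlation between blocks. The difference of two changes has variance 4(1 − r1). The post-block difference adjusted for the block-baseline difference has variance 2(1 − r2)[1 − ((r1 − r2)/(1 − r2))²]. With N = 32 and an assumed effect of 0.5 SD:

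| r1 / r2 | V change | V adjusted | power change | power adjusted | gap (points) |
|---|---|---|---|---|---|
| 0.5 / 0.5 | 2.00 | 1.00 | 49% | 78% | 29 |
| 0.7 / 0.5 | 1.20 | 0.84 | 70% | 85% | 14 |
| 0.8 / 0.5 | 0.80 | 0.64 | 86% | 93% | 6 |
| 0.9 / 0.5 | 0.40 | 0.36 | 99.1% | 99.5% | 0.4 |

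In the first row the fitted slope is (r1 − r2)/(1 − r2) = 0. The gain there comes entirely from no longer subtracting the baselines.

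**6. Carry-over into session 14.** I simulated equal correlations of 0.5 and a true effect of −0.50, with half of the active effect still present at session 14 in those who had active stimulation first. If that half persists to the end of block 2, the difference of changes estimates −0.50 and the block-baseline adjustment −0.37. If it fades before the block 2 post value, the difference of changes gives −0.62 and the adjustment −0.50.

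**The case against.** The strongest reply is that the mixed model comes first in the section, its terms are not given, and a covariate list is commonly left to the analysis plan. Analysing changes by mixed model need not mean that change scores are the response. A longitudinal model with a baseline covariate or a common baseline mean would recover most of the efficiency. This stands. A reader might infer that the whole primary analysis uses baseline only as a pre level; the text supports that for the ANOVA sentence alone. That sentence does, however, name a method under Primary analysis, and an analysis plan that follows it would run the change-score test. The sample size is also framed as an assessment-by-treatment interaction.

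A second reply is that the planned test is the five-measurement interaction, with 95.7% power at N = 32, where at most about 4 points remain to be gained. This also stands. A reader might take 10 or 29 points as losses from the stated 95%. They are not: the article gives no power for a two-level comparison or for active versus sham.

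A third reply is that covariate adjustment is not safe throughout a crossover. This stands for session 14, which may carry a persisting effect of block 1. Step 6 shows that neither analysis is unbiased in both cases. It does not touch session 2, which precedes all treatment.

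**Conclusion.** The point holds for the named pre/post ANOVA as a between-arm test. Its direction needs only equal pre and post variances and rho below 1. Its size rests on an assumed 1 SD effect and an unprinted correlation: at N = 32 from about 18 points at rho 0.3, through 10 at the 0.5 that reproduces the stated sample size, to 3 at 0.7 and under 1 at 0.8. If VAS and MML are very stable, little is lost. These figures compare subtracting and adjusting for the same baseline. For a block 2 response, the relevant rho is that with the more distant session 2 value.

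For active versus sham, a reader might infer a 29-point gain from adjusting for block baselines. That figure needs equal correlations within and between blocks. It falls to 14 at 0.7/0.5, 6 at 0.8/0.5 and 0.4 at 0.9/0.5, and it ignores carry-over. The documents do not support a general preference for session 14 as a covariate.

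**What to change.** In Primary analysis, make the post-treatment values of VAS loudness, VAS distress and MML the response of the mixed model. For the between-arm comparison, enter the session 2 value of the same outcome as a fixed covariate. Report the pre/post ANOVA on change as supportive only. Name the post-treatment visits used for each outcome: Intervention description {11a} lists MML at session 12, and the primary-outcome questionnaires at sessions 11, 12 and 13.

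For active versus sham, do not use the session 14 value, or a participant mean that includes it, as a covariate without regard to carry-over. Report the contrast of post-block values with and without the block baselines as a sensitivity analysis, and comment on any disagreement.

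The cost is one degree of freedom and analysis-plan wording. The session 2 values are already collected. The between-arm estimate is then read as a baseline-adjusted difference, and mean changes can still be reported.

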#### Secondary analysis

Regarding the EEG outcomes, pre-to-post induced changes in EEG resting-state patterns and ERP data will be analyzed. Analysis will be performed in MATLAB Software (Mathworks, Natick, MA) [46], in FieldTrip toolbox [88]. This encompasses preprocessing, power, and connectivity analyses.

### Interim analyses {21b}

No interim analyses are scheduled for this trial.

### Methods for additional analyses (e.g., subgroup analyses) {20b}

Each intervention group will also be compared separately using LME and respective post hoc tests when necessary. This will be to observe the effect of HD-tRNS alone and bimodal stimulation (HD-tRNS and AS associated).

### Methods in analysis to handle protocol non-adherence and any statistical methods to handle missing data {20c}

Efficacy analyses will be performed according to the intention-to-treat principle. The participants will be analyzed in the treatment arms to which they were randomized, irrespective of whether they refused or discontinued the treatment, or whether other protocol violations occurred. Since the questionnaires are collected electronically and each item is mandatory for questionnaire completion, we expect a low number of missing data. The other self-report assessments are also carried out electronically by standard, so that the number of missing data should also be low here. Should missing data nevertheless occur, this will be handled as follows:

The missing numerical data will be filled according to the average value of all participants or a more fitting procedure of data imputation depending on the specific issue (e.g., median or *k* nearest neighbor). Non-numerical missing data are listed as missing data accordingly.

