### Criteria for discontinuing or modifying allocated interventions {11b}

Given the general low risk associated with the study procedures, no realistic scenario of withdrawal or discontinuation can be drawn for this study. Although risk is not commonly reported with the current therapy, participants will be monitored in case they experience any symptoms. The probability exists for some minor side effects exists, as reported in the literature, such as nausea, tingling, headache, tiredness or irritating sensation, difficulty in concentration, redness, or pain [18].

In any case, participants may terminate their participation in the study at any time and without any justification. They will be registered as dropouts and will not be taken into account in the analysis.

All participants will be informed in writing on the information sheet and on the informed consent form, and verbally in the interview prior to enlisting in the study, that they may terminate their participation in the study at any time and without justification. After withdrawal, the participants will be contacted for a debriefing interview. Dropouts will be replaced in order to achieve the intended sample size whenever possible. Replacement will be performed along the established selection and allocation criteria.

Compliance is usually high, as has been observed in former studies of our group [70, 71], and other groups in the field of tinnitus research. This is true even in the absence of monetary incentives and possible detrimental effects on the condition. Therefore, no specific measures are considered to increase compliance.

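### Filling missing primary outcomes with the mean of all participants pulls the contrasts toward zero; how far depends on whether dropouts are analysed, on which the protocol contradicts itself

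*Protocol article*

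**What the plan says.** The rule is in the section on non-adherence and missing data {20c}: "The missing numerical data will be filled according to the average value of all participants". The sentence goes on to allow an alternative, "or a more fitting procedure of data imputation depending on the specific issue", with the median and k nearest neighbour as examples. Nothing says how, when or by whom the alternative is chosen, or whether the average is taken per visit, block, arm or condition. The section expects few missing values because the electronic forms require every item.

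Three other statements decide how much the rule matters:

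- The same section keeps participants in their randomised arm "irrespective of whether they refused or discontinued the treatment, or whether other protocol violations occurred".
- The section on discontinuing or modifying interventions {11b} says of those who leave: "They will be registered as dropouts and will not be taken into account in the analysis". It adds: "Dropouts will be replaced in order to achieve the intended sample size whenever possible".
- The sample size section {14} recruits 40 rather than 32 participants "to compensate for a high estimated dropout rate of up to 25% during treatment".

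The primary analysis of the two VAS ratings and MML is "frequentist linear mixed-effect modelling (LME) by the biometrician after data collection has been completed".

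**The concern.** In this design block 2 reverses the HD-tRNS condition of block 1. A missing block 2 value filled with the average of everyone is the same number whether the participant was then on active or sham stimulation, and whether in group A or B. Each such value pulls the compared means together. It also discards what the participant's own block 1 values say, although within-person comparison is the reason for a crossover. Because a filled value enters as if measured, the standard error takes no account of the imputation.

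The alternative does not repair this. The median over all participants has the same fault. Nearest-neighbour filling may do better or worse depending on what it matches on, which is not stated. Both are normally single imputations. A choice left to the specific issue can be made after the data have been seen.

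The filling is also unnecessary. A linear mixed model can be fitted to every observed value without completing the rows, and is then valid if data are missing at random. At stake is the size of the estimated effect on all three primary outcomes.

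**Working it through.** **Inputs.** From the protocol: 40 participants, 20 per arm; dropout up to 25%; block 2 in the opposite condition; the filling rule. Assumed: values missing at random, equal numbers in each order, a mean pooled over arms and conditions, and simple mean contrasts in place of the full mixed model.

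**The plan's own figure.** The protocol gives no figure for imputation bias. Its total of 32 reproduces with a within-person correlation of 0.5 and no sphericity correction (neither is stated): power is 0.957 at 32 and 0.943 at 30. At the dropout ceiling, 40 × 0.25 = 10 participants leave, 5 per arm.

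**Case 1: both compared cells lose a share d.** Let the true means be δ and 0. The pooled mean is δ/2. After filling, the cells have means (1 − d)δ + dδ/2 and dδ/2, so the difference is (1 − d)δ. At d = 0.25 it is 0.75δ, a 25% shrinkage. Simulation with 20 per arm gave 0.747.

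**Case 2: only one cell loses data.** With 15 observed against 20, the pooled mean is 15δ/35 = 0.429δ. The filled cell has mean 0.75δ + 0.25 × 0.429δ = 0.857δ, a 14% shrinkage.

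**Case 3: crossover, only block 2 lost.** The block 2 mean over both orders lies halfway between active and sham. Each condition is seen half in block 1 (complete) and half in block 2 (share d filled), so each condition mean moves by dδ/4 toward the other. The difference is δ(1 − d/2). At d = 0.25 it is 0.875δ, a 12.5% shrinkage; simulation with 40 participants gave 0.874. If both blocks are lost, Case 1 applies (simulated 0.749).

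| Share missing | Both cells lose it | Only block 2 loses it |
|---|---|---|
| 2% | 2% shrinkage | 1% |
| 5% | 5% | 2.5% |
| 10% | 10% | 5% |
| 25% | 25% | 12.5% |

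**What removes the bias.** Filling with the mean of the same condition, or using observed values only, kept about 1.00 of the effect.

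**Inference.** In the two-arm simulation with 25% missing in both arms and a true difference of 0.8 SD, the reported standard error after filling was 0.275. Complete data on 20 per arm would give √(2/20) = 0.316, and the 15 observed per arm give √(2/15) = 0.365. Estimate and standard error shrink together (0.365 × 0.75 = 0.274), so the test hardly changes: power was 0.563 with filling and 0.561 without, and type I error 0.0495. The confidence interval is too narrow and centred on the wrong value.

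In the crossover with a quarter of block 2 missing and a true effect of 0.40 SD, the filled estimate was 0.35. The effect on power depends on the unstated within-person correlation:

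| Correlation | Power, observed pairs | Power, filled |
|---|---|---|
| 0.5 | 0.56 | 0.58 |
| 0.7 | 0.77 | 0.72 |
| 0.8 | 0.92 | 0.83 |

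Type I error stayed near 5%.

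**The case against.** The strongest reply is that the large figures will not arise. Section {11b} takes dropouts out of the analysis and replaces them where it can, so only isolated gaps would be filled. Few are expected, and missed forms are chased by phone and email. The 25% is a ceiling on dropout, not a rate of missing values. Mean filling is only the first of several permitted methods, and a sensible analyst could choose a better one or average within condition, which causes no shrinkage.

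Much of this stands. A reader might infer that the plan will shrink the effect by 12.5-25% at its planned dropout rate. The documents do not support that: it needs dropout at the ceiling, dropouts kept and filled, and a mean pooled over conditions. Nor do the calculations show false positive findings, and power is lost only where within-person correlation is high.

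Three things remain. First, {20c} says the opposite of {11b} about people who discontinue, so a reader cannot tell which figure applies; relying on {11b} means giving up the intention-to-treat analysis that {20c} promises. Second, mandatory electronic items prevent gaps within a form. They do not prevent missed visits, and they do not cover MML, a primary outcome measured audiologically. Third, freedom to choose another method without a criterion is a weakness in itself and does not withdraw the rule named first.

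**Conclusion.** The point holds in a conditional form. The first-named rule is a poor one: read as written, it biases treatment contrasts toward zero and treats filled values as data, when the planned model needs no filling.

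- **Dropouts kept and filled, dropout at 25%:** shrinkage of 12.5% (active-sham contrast, block 2 only) to 25% (both compared cells). These are upper figures.
- **Dropouts left out:** about 1-5%, on an assumed 2-5% of sporadic missing values, with intention-to-treat not followed.

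Both ranges assume values missing at random and a mean pooled over arms and conditions. The main harm is a biased estimate with too narrow an interval. Whether repeated-measures ANOVA should stand beside the mixed model is a separate question and not part of this point.

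**What to change.** 1. Reconcile {11b} and {20c}: state once whether participants who discontinue are analysed. If intention-to-treat is meant, delete the sentence in {11b} that leaves them out.
2. Delete mean, median and nearest-neighbour filling for VAS loudness, VAS distress and MML.
3. State that the mixed model is fitted to all observed values without imputation, and that this rests on data being missing at random.
4. Fix one sensitivity analysis for missing data in advance, for example multiple imputation using arm, condition, block and earlier outcomes.

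No new data, visits or participants are needed. The cost is a change of wording and a little extra analysis, settled before the allocation is unblinded.
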